*Modifiable risk and protective factors*. Risk and protective factors for mental illness include resilience as measured by the Connor-Davidson Resilience Scale short form [CD-RISC (89); 2 items; range 0–8], emotion regulation competencies [German version of the Assessment of Emotion Regulation Skills; SEK-27; State Version (90); 27 items; range 27–108], self-compassion [Self-Compassion Scale; SCS-D (91); 12 items; range 12–60], self-esteem as measured by the Rosenberg Self-Esteem Scale [RSES (92); 10 items; range 10–40], and locus of control as measured by the Short Scale for the Assessment of Locus of Control [IE-4 (93)]. The IE-4 consists of two subscales for internal and external locus of control, each consisting of two items (range 2–10). Personal beliefs about the controllability and the harmful and positive nature of stress will be assessed using the Beliefs about Stress Scales’ [BASS (94)] subscales for positive (four items; range 4–16), negative (eight items; range 8–32), and controllability beliefs (three items; range 3–12).

*Health economic measures*. Indirect costs due to presenteeism and absenteeism will be assessed using the productivity loss subscale of the Trimbos/iMTA questionnaire for costs associated with psychiatric illness [TiC-P (95)], which was adapted to the context of distant-learning students in tertiary education. With this questionnaire, participants register approximations of their working hours at university, household work, and monthly salaries when holding a job besides their studies. Indirect costs, such as the number of “work loss” days (absenteeism from work) or the number of “work cut-back” days (reduced productivity at work), can be assessed.

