### Statistical Analyses

*Clinical evaluation*. Analyses based on the ITT principle will be conducted, with missing data imputed using a Markov chain Monte Carlo multivariate imputation algorithm with 100 estimations per missing.

The hypothesized superiority of the Internet-based stress intervention will be tested with regard to i) change in participants’ scores of depression and secondary outcomes from baseline (T0) to post-intervention (T1) and 3-month follow-up (T2), ii) the amount of participants with treatment response, iii) the amount of participants who experienced symptom deterioration throughout the trial, and iv) the number of individuals who achieved clinically relevant amelioration of symptoms in the IG compared to the CG.

Differences in the change of symptoms between study arms will be assessed using univariate analysis of covariance with scores at baseline used as covariate. Changes in within-group scores between baseline, T2, and T3 will be explored. Effect sizes (Cohen’s *d*) will be calculated based on the imputed data set for between- and within-group changes with 95% CIs (105). To mitigate the risk of type I error inflation due to multiple testing, *p*-values will be adjusted using Holm’s method (106).

To ascertain the number of participants attaining a reliable improvement in depressive symptomatology, participants will be coded as responders or non-responders according to the widely used *Reliable Change Index* [RCI (107, 108)]. To assess the clinically relevant impact on depression for the IG compared to control, we will calculate and compare the number of participants who achieved a reduction of >50% in depressive symptoms compared to baseline at both T1 and T2.

Negative effects of the intervention will be evaluated by the number of participants with reliable deterioration concerning depression scores through the RCI.

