*Moderators of treatment effects*. To assess the effect of putative moderators on changes in outcomes (i.e., T0 – T1), an ordinary least squares (OLS) regression-based framework for estimating interactions in moderation models will be used, along with simple slopes for probing interactions. In order to test the robustness of our findings and to examine differences between imputed data and complete cases, separate sensitivity analyses (109, 110) will be conducted. Moreover, to assess relevant subgroup effects, follow-up simple slope analyses for possible significant interaction effects will be conducted. The slope and significance of the intervention main effect will be evaluated for conditional values (one standard deviation below and one standard deviation above the mean) of the moderator (111). For more precise information on conditional effects of the moderators, the Johnson–Neyman technique will be applied (112).

*Cost–benefit evaluation*. According with common practice, a probabilistic approach will be used to make health-economic inferences (113). The total benefit of the intervention will be derived by subtracting productivity loss costs assessed by the TiC-P of the CG from the ones of the IG. The cost–benefit relationship will be reported by calculating the three most frequently used metrics: i) the net benefits (NB), the net monetary gain of the intervention; ii) the benefit–cost ratio (BCR), the money saved for one monetary unit invested; and iii) the return-on-investment (ROI), indicating the percentage of profit with every monetary unit invested. Bootstrapped 0.95% CIs with 2,500 replications will be estimated around these metrics.

Sensitivity analyses will be conducted to assess the robustness of the findings and to account for uncertainty regarding the actual prize of implementing the intervention into health care. Further health economic analyses will be conducted if feasible.

*Help-seeking behavior analysis*. To make assertions on the help-seeking intentions and behaviors of participants, baseline data of all participants from the GHSQ-Per-Emot (96), eHEALS (97), “awareness of online counseling,” and “reasons for participation” questionnaires will be analyzed using descriptive statistics.

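### The cost–benefit paragraph defines benefit as intervention-group minus control-group losses, so a saving counts as negative, and it prints the interval level as 0.95%

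*Protocol article*

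**What the plan says.** The cost–benefit evaluation has its own paragraph under Statistical Analyses in the protocol article. It states that the total benefit is "derived by subtracting productivity loss costs assessed by the TiC-P of the CG from the ones of the IG". It then names three metrics built on that benefit:

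- net benefits (NB): "the net monetary gain of the intervention";
- benefit–cost ratio (BCR): "the money saved for one monetary unit invested";
- return on investment (ROI): "indicating the percentage of profit with every monetary unit invested".

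On uncertainty it says: "Bootstrapped 0.95% CIs with 2,500 replications will be estimated around these metrics".

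The measured quantity is described in the health economic measures paragraph under Secondary Outcomes: "Indirect costs due to presenteeism and absenteeism will be assessed using the productivity loss subscale". It is therefore a cost, and lower is better. Nothing else in the article restates or corrects the benefit formula. For effect sizes, the clinical evaluation paragraph of the same section uses the conventional level: "between- and within-group changes with 95% CIs (105".

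**The concern.** Subtracting the CG's costs from the IG's means IG minus CG. If the intervention works as hypothesised, the IG loses less productivity than the CG, and the quantity named as the benefit comes out below zero. The three metrics are worded as a gain, a saving and a profit, so they need a benefit that is positive in exactly that case. The formula and the definitions cannot both hold.

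Health-economic benefit is the fourth aim at the end of the Background, and this paragraph is the only place where the benefit is defined. Study Design promises that the analysis scripts will be made public. Scripts that follow the formula would give a wrongly signed benefit. Scripts that follow the definitions would depart from the published formula without explanation.

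The interval level is a separate slip in the same paragraph. A 0.95% interval is not a usable statement of uncertainty.

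**Working it through.** The plan gives no cost figures and no computed benefit, so there is no figure of its own to reproduce. The check is of sign and algebra, followed by an illustration on assumed costs.

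**Algebra.** Let S = CG costs − IG costs (the saving, positive when the intervention helps) and let C be the cost of the intervention. The usual forms of the three verbal definitions are NB = B − C, BCR = B/C and ROI = 100 × (B − C)/C, where B is the benefit.

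| | As printed, B = IG − CG = −S | As the definitions require, B = CG − IG = S |
|---|---|---|
| NB | −S − C | S − C |
| BCR | −S/C | S/C |
| ROI | −100 × (S + C)/C | 100 × (S − C)/C |

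The sign of B and of BCR reverses for every nonzero S, whatever the costs are. NB and ROI do not simply change sign, because C is subtracted in both columns. Negating the printed NB gives S + C, which differs from S − C by 2C. Negating the printed ROI leaves it 200 percentage points too high.

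**Illustration.** Assumed: CG costs 1,000 and C = 100, with three values for the IG.

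| IG costs | S | Version | B | NB | BCR | ROI |
|---|---|---|---|---|---|---|
| 700 | 300 | printed | −300 | −400 | −3.0 | −400% |
| 700 | 300 | corrected | +300 | +200 | 3.0 | +200% |
| 950 | 50 | printed | −50 | −150 | −0.5 | −150% |
| 950 | 50 | corrected | +50 | −50 | 0.5 | −50% |
| 1,300 | −300 | printed | +300 | +200 | 3.0 | +200% |
| 1,300 | −300 | corrected | −300 | −400 | −3.0 | −400% |

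- First case: a saving larger than the cost is reported as a loss.
- Second case: the saving is below the cost, so NB and ROI are negative either way. They are still misstated, by 100 in NB (−150 against −50).
- Third case: extra losses in the IG are reported as a profit.

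**Interval level.** A central interval of 0.95% has a normal quantile of 0.0119, against 1.960 for 95%. The ratio is 1.960/0.0119, about 165. In percentile terms with 2,500 replications, 0.95% runs from about rank 1,238 to rank 1,262, and 95% from about 62.5 to 2,437.5.

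**The case against.** The strongest reply is that the paragraph exposes its own slip. The result is called a benefit, and the next sentence speaks of gain, saving and profit. An analyst who implements those definitions will use CG minus IG. Likewise, 0.95% is plainly 0.95 or 95% mistyped, since the section uses 95% elsewhere and the sample-size paragraph sets alpha at 0.05. The evaluation is also peripheral: the abstract treats it as additional, and the Discussion says that the power limitation extends to it.

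Most of this stands. The intended direction can be inferred, and the factor of 165 describes an interval that nobody is likely to compute, so it adds no practical weight. It does not remove the error. A stated analysis rule contradicts the definitions beside it, and the sentence is complete and unambiguous as printed.

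A reader might infer three stronger things that the article does not support:

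- *All three metrics are damaged beyond repair.* BCR is restored by a plain change of sign. NB and ROI can be recovered once C is known: the correct NB is −(printed NB) − 2C, which gives 400 − 200 = +200 in the first case.
- *The economic conclusion always reverses.* It does not when the saving is smaller than the cost.
- *The published scripts will carry the error.* Nothing in the article shows how the analysis is coded.

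**Conclusion.** The point holds as an error of wording in a stated analysis rule. Read literally, the benefit and BCR have the wrong sign for any cost difference. NB is −S − C instead of S − C, with ROI misstated correspondingly. An intervention whose saving exceeds its cost would be reported as a loss. Where the saving is below the cost, NB stays negative but has the wrong size. The interval level is wrong as printed and conflicts with the 95% used in the same section.

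The sign result rests only on the printed formula and on productivity losses being costs. The NB and ROI results also rest on the usual forms of those metrics, which the article defines in words only. The monetary figures are assumptions for illustration.

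The reach is limited to the secondary health-economic evaluation under the fourth aim. It would be wrong to read the slip as touching the primary outcome, the sample size or the clinical analyses.

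**What to change.** Make two changes in the cost–benefit paragraph:

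1. State that the total benefit is the productivity-loss costs of the CG minus those of the IG.
2. Change 0.95% CIs to 95% CIs.

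No new metric formulas are needed, because the verbal definitions of NB, BCR and ROI are consistent once the subtraction is turned round. The article does not say whether the intervention's cost is to be taken net of the CG programme's cost, and this correction does not require that to be settled. Check that the scripts to be made public use the same direction and level. The cost is two edits to the text, with no new data, participants or change of design.

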## Discussion

This protocol describes the rationale and design of a two-armed RCT evaluating the effectiveness, moderators, and health economic outcomes of an Internet- and App-based stress intervention for distance-learning students. We hypothesize the intervention to be more effective in reducing symptoms of depression and improving other mental health-related outcomes when compared to a CG receiving Internet-based psychoeducation.

The relevance of early intervention in mental health promotion and prevention has become increasingly evident in recent years (42, 114). Easily accessible and acceptable instruments are urgently needed when facing discouragingly low utilization rates found for conventional health promotion approaches directed at the general public (115). This trial will contribute to the ongoing investigation into the potential of Internet-based interventions to reach out to individuals who would not otherwise seek treatment due to psychological barriers. Furthermore, this study will explore moderators of intervention effects and assess the intervention’s health economic potential when implemented into routine care. Help-seeking behavior will be assessed to attain more knowledge on the causes and motivation of distance-learning students when seeking help *via* the Internet.

This trial will employ a cutoff for elevated symptoms of depression, although not restricting eligibility to individuals showing symptoms of full-blown depression only. Although in its content, the intervention at hand focuses on academic stress, we did not decide for a cutoff for perceived stress, as this trial is aimed at evaluating the intervention’s effectiveness as an intervention instrument in individuals with an indicated risk for depression and in individuals potentially suffering from major depression. Perceived stress has been associated with the development (33) and worse trajectories (34, 35) of clinical depression. The potential of Internet-based stress interventions as an early intervention and treatment instrument in depressive target groups, however, has not yet been evaluated. Mental health stigma, a known barrier to treatment utilization, has been shown to be greatest among highly distressed individuals with low depression literacy (116). If the intervention evaluated in this trial is found to be effective, Internet-based stress interventions could be investigated as a potential mean to address depression in individuals for whom a conventional mental health disorder treatment would not be an option.

We will compare the effects of the intervention to an Internet-based psychoeducation program of similar length. Meta-analytic evidence suggests that Internet-based interventions for college students show moderate to large effect sizes when compared to a waiting CG. This superiority, however, could not be ascertained when compared to active CGs (117). Treatment expectancies have been discussed as an artifact in clinical evaluation studies utilizing waitlist CGs. Participants waiting for treatment may be less motivated to initiate health-related behavior changes (118–120), which could over-accentuate effects attributed to an intervention (120, 121). Findings in this trial will provide the opportunity to investigate the effects of an Internet-based intervention employing evidence-based cognitive–behavioral techniques compared to a CG in which participants are also actively engaged.

Findings of this trial will have some limitations. First, an open recruitment strategy is employed, in which potential participants are actively recruited from the student population. Therefore, we cannot rule out selection bias, with more motivated individuals attaining access to the study. Second, due to feasibility reasons, this trial is somewhat underpowered to reliably detect significant treatment moderators. This might impede finding statistically significant factors contributing to this interventions’ effectiveness that would have been detected in a larger study sample (122, 123). Same applies to health-economic inferences, for which a probabilistic approach will be applied in this study. Third, due to logistic reasons, this trial will only use self-administered questionnaires and will not assess diagnostic status or physiological measures.

There is a growing number of studies investigating the efficacy of Internet-based interventions in reducing various symptoms of mental illness (124, 125). Much less is known, however, on the potential of such interventions in distance-learning student samples, and their impact on academic functioning, for which this study will provide tangible empirical results. Results will also provide the opportunity to investigate the practicability of Internet-based stress interventions as an approach to address mental health issues in individuals with subthreshold or full-blown symptoms of depression and increase their use of health services.

### Trial Status

Recruitment started in April 2017. Follow-up assessments for the last participant are expected to be completed by March 2019.

## Ethics Statement

All procedures involved in the study are consistent with the generally accepted standards of ethical practice. All potential participants have to provide written informed consent to be eligible for study inclusion. The study was approved by the University of Erlangen-Nuremberg ethics committee (Erlangen, Germany; 33_17 Bc).

## Abbreviations

CG, control group; CONSORT, Consolidated Standards of Reporting Trials; IG, intervention group; ITT, intention to treat; RCI, Reliable Change Index; RCT, randomized controlled trial; SPIRIT, Standard Protocol Items: Recommendations for Intervention Trials; T0, baseline; T1, post-assessment (7 weeks after randomization); T2, 3-month follow-up (3 months after randomization).
